### Clinical characteristics

A routine physical examination by a physician will be performed. Medical history, medications, smoking status, allergy status, exacerbation history, infection status, blood pressure, heart rate and SpO_2_, and electrocardiogram (ECG) in supine position will be recorded.

Bioimpedance.

To assess body composition, bioimpedance is used to estimated body fat and lean muscle mass.

### Questionnaires

COPD specific questionnaires will be used to identify symptom burden and health-related quality of life (HRQoL). The COPD Assessment test (CAT) is an 8-item, validated questionnaire, with good discriminant properties. The scoring ranges from 0 to 5 points for each question, i.e., resulting in a total score of 0–40, and with a lower the score indicating better health status. A change of 2 units has been used as a minimal clinically important difference (MCID) [21].

Clinical COPD questionnaire (CCQ) is a HRQoL questionnaire. It includes 10 questions about the participants well-being the last week scoring from 0 (= never) to 6 (= almost all the time) a total score of (0–60)/10, and with a lower the score indicating better health status [22]. A change of 0.4 units has been used as a MCID [23]. Modified Medical Research Council (mMRC) scale measures dyspnea. It measures dyspnea in 5 steps (0–4) with 0 being the least and 4 being the most dyspnea [24].

### Exercise tests

#### Six-minute walk test (6MWT)

The six-minute walk test (6MWT), a sub-maximal exercise test, is used to assess aerobic capacity and endurance [24]. In the 6MWT, the subjects are asked to walk, in a 30-meter distance, as far as possible during six minutes. The following parameters will be observed: walking distance, SpO_2_, heart rate, perception of dyspnea and leg fatigue every two minutes during the test [25]. The 6MWT will be performed twice at the baseline visit, and the results from the best performance (= longest distance) is used. The MCID is 30 m [25, 26].

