### Secondary outcomes

The secondary outcomes are to validate the effect of training to:

Identify responders and non-responders based on measurements of vital lung parameters (e.g., IOS, FEV_1_, DLCO, AiDA) and physical capacity (6MWT, sit-to-stand test) after exercise intervention.Identify changes in biomarkers related to regenerative processes, matrix turnover, stem/progenitor cell activity, and inflammatory patterns in lung tissue biopsies, blood- and urine samples, and correlate these changes with vital lung parameters (e.g., IOS, FEV_1_, DLCO, AiDA) and measures of physical capacity (e.g., 6MWT, sit-to-stand test).To validate the effect of the exercise intervention on vital lung parameters based on established and novel lung function measurements e.g., IOS, spirometry, DLCO, AiDA, Cardiopulmonary exercise testing.To validate the effect of the exercise intervention on the physical capacity based on established measurements 6-MWT, sit-to-stand test.

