### Study procedures

At first visit, all subjects will initially go through a clinical examination including electrocardiogram. Before first measurement the subjects will inhale 400 µg short acting beta-2 agonist (salbutamol, Buventol^®^ Easyhaler) using a valve spacer device. All testing will be performed at least 15 min thereafter in the following order: fractional exhaled NO (FeNO), 6MWT, IOS, Spirometry, Body plethysmography, DLCO, SBW, 1-minute sit-to-stand test, 6MWT no 2 (at baseline visit), Cardiopulmonary exercise testing (CPET) - which might be done at a separate visit. Subjects will be asked to rest when needed between tests, and specifically at least 10–15 min after 6MWT and sit-to-stand test. If the subject fulfills any of the exclusion criteria, no further testing will be performed.

Blood and urine samples will be taken, and questionnaires will be filled in during resting times. Aida will be done on a separate visit.

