### Order of assessments and procedures during study visits

The order of assessments and procedures during each study visit has been standardised to ensure consistency and minimise participant burden. At each visit, procedures will be conducted in the following sequence: Fractional exhaled NO (FeNO), 6MWT, IOS, Spirometry, Body plethysmography, DLCO, SBW, sit-to-stand test, 6MWT no 2 (at baseline visit), Cardiopulmonary exercise testing (CPET), which might be done at a separate visit. Subjects will be asked to rest when needed between tests, and specifically 10–15 min after 6MWT and sit-to-stand test. Blood and urine samples will be taken and questionnaires will be filled in during resting times. Aida will be done at a separate visit.

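### The six-minute walk is scored as the longer of two walks at baseline but as a single walk at 12 weeks, which tends to understate the training gain

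*Protocol article*

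**What the plan says.** The section on the six-minute walk test (6MWT) sets the baseline rule: "The 6MWT will be performed twice at the baseline visit, and the results from the best performance (= longest distance) is used". It also states "The MCID is 30 m".

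Two sections fix when the second walk takes place. Study procedures lists "1-minute sit-to-stand test, 6MWT no 2 (at baseline visit". Order of assessments and procedures during study visits opens with "At each visit, procedures will be conducted in the following sequence" and then lists "sit-to-stand test, 6MWT no 2 (at baseline visit), Cardiopulmonary exercise testing (CPET), which might be done at a separate visit". Both confine the second walk to baseline. The visible text gives neither a second walk at 12 weeks nor another scoring rule for that visit. The schedule figure is not shown.

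Under Secondary outcomes the 6MWT serves three purposes: the training effect ("To validate the effect of the exercise intervention on the physical capacity based on established measurements 6-MWT, sit-to-stand test"), the separation of responders from non-responders ("physical capacity (6MWT, sit-to-stand test) after exercise intervention"), and correlation with biomarker changes. The article gives no test-retest SD, learning effect or expected change for the 6MWT.

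**The concern.** The baseline value is the maximum of two attempts and the follow-up value is one attempt, so the within-person change compares unlike quantities. Chance alone makes the better of two walks longer, on average, than a single walk. Any gain from having walked the course once already adds to the baseline value and may or may not still be present 12 weeks later.

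This is a single-arm trial, so no control group carries the same asymmetry and cancels it. At stake are the estimated change in walking distance and, if responders are defined by a distance cut-off, how many participants reach it.

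**Working it through.** **Inputs from the protocol article.** Two walks at baseline with the longer used; one walk at 12 weeks; MCID 30 m; 80 participants with 10–20% drop-out, hence 64 to 72 completers.

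**Assumed inputs, not in the documents.** Test-retest SD *s* of 15–30 m; learning gain *L* from walk 1 to walk 2 of 0–30 m; share *f* of that gain present at 12 weeks, from 0 (lost) to 1 (kept), with 1.5 for learning that continues beyond walk 2. Errors are independent and normal. The protocol has no figure of its own to reproduce here.

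**Formula.** Measure distances from a participant's unpractised baseline level. Walk 1 has mean 0 and walk 2 has mean *L*. The 12-week walk has mean (true gain + *fL*). With *a* = *L*/(*s*√2),

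E[max] = *L*·Φ(*a*) + *s*√2·φ(*a*), and the understatement of the gain is E[max] − *fL*.

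**No learning (*L* = 0).** The expression reduces to *s*/√π = 0.564*s*:

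| *s* (m) | 15 | 20 | 25 | 30 |
|---|---|---|---|---|
| understatement (m) | 8.5 | 11.3 | 14.1 | 16.9 |

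**With learning, in metres:**

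| *L*, *s* | kept (*f* = 1) | lost (*f* = 0) |
|---|---|---|
| 20, 15 | 2.0 | 22.0 |
| 20, 30 | 8.8 | 28.8 |
| 30, 15 | 0.8 | 30.8 |
| 30, 30 | 6.0 | 36.0 |

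**Comparison of the possible contrasts.** The expected error in the gain is +*fL* using walk 1, −(1 − *f*)*L* using walk 2, and *fL* − E[max] under the protocol's rule. For *L* = 20 and *s* = 20, *a* = 0.707 and E[max] = 20 × 0.760 + 28.28 × 0.311 = 24.0 m:

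| *f* | walk 1 | walk 2 | protocol's maximum |
|---|---|---|---|
| 0 | 0 | −20 | −24.0 |
| 0.5 | +10 | −10 | −14.0 |
| 1 | +20 | 0 | −4.0 |
| 1.5 | +30 | +10 | +6.0 |

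For *f* between 0 and 1, the walk-1 and walk-2 contrasts enclose the true gain in expectation, and the protocol's contrast lies below both. If learning continues beyond walk 2 (*f* = 1.5), all three overstate the gain.

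**Responders, as an illustration.** The article states no cut-off. Assume 30 m, with a true gain of mean 30 m and SD 30 m, and *s* = 20 m. By simulation with 1,000,000 draws, the share reaching the cut-off is 39% with no learning, 46% with 20 m of learning kept and 27% with it lost, against 50% on the true gain.

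**Scale.** For an assumed SD of change of 40–60 m, the standard error of the mean change is between 40/√72 = 4.7 m and 60/√64 = 7.5 m. With no learning the understatement exceeds that; with learning kept it is of similar size or smaller.

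**The case against.** The strongest defence is that the second baseline walk is deliberate. Without a control group, a practice walk keeps retained learning from being credited to training, and any remaining downward error is conservative for a claim of benefit. This justifies having a practice walk and comparing walk 2 with the 12-week walk. It does not justify taking the maximum, which adds a downward error even when all learning is kept.

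Two further objections stand. The direction is conditional, because learning that continues beyond walk 2 can turn the error upward. The outcome is also one of several secondary measures in a hypothesis-generating study whose primary outcome is protein profiles.

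A reader might infer three stronger claims that the documents do not support:

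- **The error rivals the 30 m MCID.** Without learning this needs a test-retest SD of 30 × √π = 53 m. Otherwise it needs roughly 20–30 m of learning that has wholly vanished by 12 weeks. The documents supply neither.
- **Correlations with biomarkers are distorted.** A constant shift leaves a correlation unchanged. Without learning, the maximum has error variance (1 − 1/π)*s*² = 0.68*s*², below the *s*² of a single walk.
- **Responders are certainly missed.** Secondary outcomes states no 6MWT cut-off and does not tie response to 30 m.

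**Conclusion.** The point holds as a difference in scoring rules between the two visits, settled by the visible text. It tends to understate the training gain whenever the learning still present at 12 weeks does not exceed that reached by walk 2. Responder counts would fall with it if a distance cut-off is used.

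The documents do not allow the size to be fixed. Under the assumed SDs of 15–30 m it is about 8–17 m with no learning and about 1–9 m with 20–30 m of learning fully kept. It reaches 22–36 m only if all of that learning is lost. The point deserves correction because the rule gives a biased secondary outcome and a less biased reading needs no new procedure.

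**What to change.** Stop using the maximum of the two baseline walks for the change score. Pre-specify:

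1. **Main contrast:** baseline walk 2, the walk after familiarisation, to the 12-week walk.
2. **Other bound:** baseline walk 1, which holds the same place in the test sequence, to the 12-week walk, reported alongside.
3. **Responders:** if the 6MWT enters the classification, use the main contrast there too.

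This adds no test and can be applied to participants already assessed. It assumes that both baseline distances are recorded. The article does not say so outright, but choosing the longer one implies it. The cost is a slightly noisier baseline: without learning, error variance *s*² in place of 0.68*s*².

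Do not adopt best-of-two at both visits without this bracketing. It removes the selection effect, but retained learning would then be credited to training. With *L* = 20 m fully kept, the overstatement is *L* + 0.564*s* − E[max]. That is 5.1, 7.3 and 8.2 m for *s* = 10, 20 and 30 m, against understatements of 0.5, 4.0 and 8.8 m under the present rule.

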#### One-minute sit-to-stand test

The one-minute sit-to-stand tests measures leg muscle strength [27]. The subject starts in a sitting position, and during one minute stands up from a chair (height 46–48 cm) and sits down again as many times as possible. The number of times to stand up is the main outcome. SpO_2_, heart rate, perception of dyspnea and leg fatigue before and after the test will be assessed [27]. The MCID is three repetitions [27].

#### Cardiopulmonary exercise testing (CPET)

Cardiopulmonary exercise testing (CPET) is a method for standardized testing of exercise capacity and will be performed during cycling. In short, during the CPET numerous components are observed: electrocardiogram changes, blood pressure readings, heart rate monitoring, gas analysis breath-by-breath (such as oxygen uptake [VO_2_] and carbon dioxide elimination [VCO_2_]), minute ventilation (V_E_) and subjective ratings of perceived exertion during every second minute during the test. There is an initial phase of breathing in the mask for 3 min, to stabilize the equipment, followed by a pedaling for 3 min without any workload. Thereafter women will start on a work load of 20 W and men at 30 W followed by a ramp increase in workload (10 W/minute) until exhaustion. We aim for a duration of 8–10 min and a minimum duration of exercise of 6 min.

The CPET is performed using an electronically braked cycle ergometer and breath-by-breath gas analysis equipment (Vyntus CPX Metabolic Cart, Vyaire Medical, Mettawa, IL, United States) for gas analysis. The data analysis is performed using SentrySuite software version 3.20 (Vyaire Medical, Höchberg, Germany) for CPET parameters. Reference values for VO_2_peak are from Gläser 2010 [28]. MCID for VO_2_ is established to 5–10% [29].

#### Fractional exhaled NO (FeNO)

Fractional exhaled NO (FeNO) is measured using an Ecomedics, CLD88 (Dürnten, Switzerland). The test starts with a maximum exhalation, then an inhalation of NO depleted air from the mouthpiece, and thereafter an exhalation at a flow of 50 ml/s. The device uses a built-in flow restrictor to maintain the exhalation flow and provides real-time visual feedback to ensure correct performance. The mean of three adequate measurements will be recorded [30].

#### Lung function tests

##### Spirometry

Flow volume spirometry will be performed to measure forced expiratory volume in 1 s (FEV_1_) and forced vital capacity (FVC). FEV_1_/FVC is calculated as a measure of expiratory flow limitation. Spirometry is performed according to ERS guidelines [31] (using a Jaeger MasterScope; Hoechberg, Germany) in an upright position with a nose clip. The best of three adequate measurements will be recorded. As a Swedish population will be investigated the reference equations from Hedenström et al. [32, 33] will be used to calculate % of predicted values.

### Impulse oscillometry (IOS)

IOS provides information about the mechanical properties of large and small airways (Jaeger MasterScreen IOSHoechberg, Germany). Resistance is estimated at 5 Hz (R_5_, reflecting total resistance) and at 20 Hz (R_20_, reflecting central resistance), while R_5_-R_20_ is subsequently calculated and reflects peripheral resistance. Airway reactance (elastance) of the lung is estimated at 5 Hz (X_5_), which during small airway obstruction gives a more negative value, while the resonant frequency (F_res_) increases together with the area under the reactance curve (AX), which is measured from 5 Hz to F_res_. The test is performed in an upright position and the subjects hold their hand palms on their cheeks to stabilize the upper shunt [34]. The mean of three accurate measurements of 30 s is recorded.

### Body plethysmography

Body plethysmography is used (MasterScreen Body, Erich Jaeger GmbH), to measure static lung volumes according to European Respiratory Society (ERS) standards [35], i.e. total lung capacity (TLC) and residual volume (RV), and the ratio RV/TLC is calculated as a measure of air trapping. In addition, total (R_tot_), inspiratory (R_in_) and expiratory (R_ex_) resistance are measured. The mean of three accurate measurements is recorded.

### Diffusing capacity of the lung

Diffusing capacity of the lung for carbon monoxide (CO) (DL_CO_), the rate constant for uptake of CO (K_CO_) and alveolar volume (VA) will be measured/calculated using the MasterScreen Pulmonary Function Test (PFT) equipment (Erich Jaeger GmbH). A single-breath carbon monoxide diffusion test is performed by a breath-hold for 10 s, according to ATS/ERS standards [36], in a sitting position and wearing a nose clip. CO and methane are used as tracer gases. The mean of three accurate measurements is recorded.

### Single breath nitrogen wash-out

Single breath nitrogen wash-out measures ventilation heterogeneity in the peripheral airways by analysing the slope of the alveolar phase of a breath. The maneuver is performed by a maximum exhalation, maximum inhalation and thereafter maximum exhalation again using an Exhalyzer D (Eco Medics, Dürnten, Switzerland). The test is performed in a sitting position and wearing a nose clip. The mean of the phase III slope (SIII) of three accurate measurements is recorded.

### Airspace dimension assessment (AiDA)

AiDA is a novel method used to measure the dimensions of the distal airspaces by analyzing inhaled and exhaled concentrations of 50 nm aerosol particles. The deposition fraction over several breath-holds is used to calculate an average distal airspace radius (r_AiDA_) and a zero-second recovery (R_0_), which is assumed to be determined by geometrical properties of the peripheral lung, such as airway heterogeneity [12, 37]. The breathing manoeuvre is similar to that used for single-breath D_LCO_, with the subject breathing into a mouthpiece while wearing a nose clip. The subjects breathe particle-free air for approximately 30 s, after which air is exhaled to residual volume and then aerosol particles are inhaled to total lung capacity. Thereafter, the subjects hold their breath for a few seconds, and then exhale. The aerosol concentration is measured from exhaled air after washout of dead space. The manoeuvre is repeated with breath-holds of 5, 7 and 10 s, with at least two successful replicates of each, for a total of at least six measurements.

The technical principle of AiDA and how the distal airspace radius, *r*_AiDA_ and the R_0_ have been described in more detail elsewhere [37]. Prior to further analysis, the adherence to the breathing manoeuvre and the stability of the particle generation will be evaluated for each measurement, and low-quality measurements will be excluded.

### High resolution computer tomography (HRCT)

High resolution computer tomography (HRCT) will be performed according to clinical routine. Emphysema will be classified as centrilobular, panlobular or paraseptal. Additional visual features to be evaluated include airway wall thickening, small airway disease, tracheal and interstitial abnormalities, pulmonary arterial enlargement and bronchiectasis [38]. Grading of emphysema will be done as volume with low and high attenuation density of the respective lung. A Specialist in Clinical physiology will quantify volumes with low and high attenuation density in the lung tissue from the HRCT pictures, by means of an objective imaging density measurement.

### Sample collection

Inflammatory biomarkers, regeneration components and cellular profiles will be investigated in blood, urine and BAL samples.

### Blood samples

All blood samples are collected before 13.00 o’clock to avoid any effect of diurnal variation. Blood will be drawn in EDTA tubes for differential cell count (performed at the hospital routine laboratory), for plasma (collecting the supernatant after 10 min centrifugation in 2000 x g) and for buffy coat (collecting the white blood cell layer after the centrifugation). In addition, serum will be sampled (after 30 min incubation to enable coagulation and collecting the supernatant after 10 min centrifugation in 2000 x g). Samples will be frozen in −80 °C until further analyses. Levels of hemoglobin and alpha-1 antitrypsin will be measured according to clinical routine.

### Urine samples

Urine will be collected and frozen in −80 °C until further analyses.

### Bronchoscopy samples

Bronchoscopy is performed in accordance with clinical routine to obtain bronchial biopsies and bronchoalveolar lavage (BAL) samples. Six biopsies are collected from the left lower lobe using the cryobiopsy technique, with a freezing time of four seconds. BAL is carried out by instilling two aliquots of 50 mL of body-temperature isotonic saline into the lingula or middle lobe, followed by gentle aspiration [39, 40].

### Participant timeline

Participants will first be contacted by phone or mail for an initial screening. Before the intervention begins, they will undergo a comprehensive baseline assessment (one to three visits). Following this, participants will engage in a 12-week supervised exercise intervention, with data collection scheduled at mid-intervention (after 6 weeks, one visit) and post-intervention (after 12 weeks, one to three visits).

The baseline and post-intervention assessments will include medication use and health status, clinical examination by a physician, collection of participant data, questionnaires, physical capacity tests, comprehensive pulmonary function assessments, and sample collection.

The mid-intervention assessment will cover medication use, health status, questionnaires, spirometry, and blood sampling.

Participant recruitment is summarized in a flow diagram (Fig. 2), and the schedule of enrolment, intervention, and assessment are presented in the SPIRIT diagram (Fig. 3).

**Fig. 2 Fig2:**
[figure not shown]
Flow diagram of participant recruitment

**Fig. 3 Fig3:**
[figure not shown]
SPIRIT diagram illustrating the schedule of enrolment, interventions and assessments

### Order of assessments and procedures during study visits

The order of assessments and procedures during each study visit has been standardised to ensure consistency and minimise participant burden. At each visit, procedures will be conducted in the following sequence: Fractional exhaled NO (FeNO), 6MWT, IOS, Spirometry, Body plethysmography, DLCO, SBW, sit-to-stand test, 6MWT no 2 (at baseline visit), Cardiopulmonary exercise testing (CPET), which might be done at a separate visit. Subjects will be asked to rest when needed between tests, and specifically 10–15 min after 6MWT and sit-to-stand test. Blood and urine samples will be taken and questionnaires will be filled in during resting times. Aida will be done at a separate visit.

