### Intervention

#### Intervention description

The 12-week exercise intervention will consist of moderate intensity aerobic and strength training twice per week as “supervised training on site” and once per week as “training at home”. All exercise sessions on site will be conducted in groups of 3–8 people in a public fitness setting and supervised by a knowledgeable and experienced physiotherapist. Supervision of exercise will include providing motivation and feedback and/or modifying exercises as appropriate/required by, for example, changing the resistance, pace or number of repetitions. The physiotherapists will adhere to a single training protocol to ensure standardized delivery of the training across centers, and regular meetings during the trial will be used to check that the procedures are carried out in the same way at both sites.

The supervised training sessions on site will include.

Aerobic exercise for 33 min on a cycle ergometer at a moderate intensity (≥ 60% Wpeak), individually tailored to achieve a perceived exertion level of 3–6 on the Borg CR-10 scale [1]: After 3 min of warm-up at a low intensity, the exercise will be performed in intervals, 2 min at a moderate intensity, 50–60 revolutions per minute (rpm), 1 min at low intensity, 2 min at a moderate intensity etcetera, in total, 10 intervals at moderate intensity. The exercise intensity will be based on symptom limitation and tailored to the individual needs and limitations of the subject. As one exclusion criterion is oxygen saturation (SpO_2_) ≤ 87% at the screening 6MWT, we do not expect that anyone will desaturate during the training. However, if SpO_2_ decreases < 85% during cycling the training will be stopped and commence when SpO_2_ > 90% [17]. If this happens more than once the patient will be excluded.Strength training for 30 min, involving seven exercises targeting major upper and lower body muscle groups. Each exercise comprises three sets with 8–12 repetitions. For the muscle strengthening exercise equipment such as graded elastic bands and handheld dumbbells will be used. The exercise load will be determined by the participant’s ability to complete 10 repetitions for a given exercise and progression will be achieved by increasing the number of sets, weight or elastic band resistance, as guided by the physiotherapist.

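### A same-day CPET comes straight after an extra six-minute walk at baseline but not at 12 weeks, and nothing stated ties a participant's two CPETs to the same day arrangement

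*Protocol article*

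**What the plan says.** The protocol article gives the test order twice. The section on the order of assessments says: "At each visit, procedures will be conducted in the following sequence: Fractional exhaled NO (FeNO), 6MWT, IOS, Spirometry, Body plethysmography, DLCO, SBW, sit-to-stand test". It then continues: "6MWT no 2 (at baseline visit), Cardiopulmonary exercise testing (CPET), which might be done at a separate visit". The Study procedures section has the same ending: "6MWT no 2 (at baseline visit), Cardiopulmonary exercise testing (CPET) - which might be done at a separate visit".

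The 6MWT section confirms that the extra walk belongs to baseline: "The 6MWT will be performed twice at the baseline visit, and the results from the best performance (= longest distance) is used".

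On rest, Study procedures asks for a minimum of 10–15 min after a walk or sit-to-stand test. The order section gives 10–15 min without calling it a minimum. Both also allow rest as needed. The participant timeline allows one to three visits at baseline and again at 12 weeks, and AiDA already has its own visit.

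The CPET section describes a workload ramp continued "until exhaustion" and gives an MCID for VO2 of 5–10%. The secondary outcomes include the effect of training on "IOS, spirometry, DLCO, AiDA, Cardiopulmonary exercise testing". The trial has a single group. The Statistical methods section plans paired tests of change for the primary outcome.

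**The concern.** A before-after comparison without a control group relies on measuring under the same conditions both times. The written order does not provide that for CPET. On a single test day, the baseline CPET comes straight after a second walk and the 12-week CPET does not.

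The option of a separate visit adds a second source of inequality. A participant could have one CPET on the main test day and the other on a fresh day, in either order, and still be within the plan.

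CPET is limited by effort, so earlier exertion can reduce peak values. With no control arm, a difference in earlier exertion cannot be told apart from a training effect. No analysis can restore equal conditions once the tests are done.

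**Working it through.** **Step 1. What precedes a same-day CPET.**

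| | Baseline | 12 weeks |
|---|---|---|
| First 6MWT, early in the session | yes | yes |
| Rest, then IOS, spirometry, plethysmography, DLCO, SBW | yes | yes |
| Sit-to-stand, then rest | yes | yes |
| Second 6MWT, then rest | yes | no |
| CPET | last | last |

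The only stated difference is one six-minute walk, and it sits immediately before CPET.

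**Step 2. Direction of the bias.** Let *Fb* be the percentage loss in VO2peak from a same-day CPET at baseline (two walks and sit-to-stand) and *Ff* the loss at 12 weeks (one walk and sit-to-stand). The loss on a separate day is 0. With *sb* and *sf* equal to 1 for same-day and 0 for separate-day testing:

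bias in the gain = *Fb*·*sb* − *Ff*·*sf*

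The documents give neither *Fb* nor *Ff*. The table uses three assumed pairs, as illustration only.

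| Baseline / 12 weeks | (2%, 1%) | (3%, 2%) | (5%, 3%) |
|---|---|---|---|
| same day / same day | +1 | +1 | +2 |
| same day / separate | +2 | +3 | +5 |
| separate / same day | −1 | −2 | −3 |
| separate / separate | 0 | 0 | 0 |

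If *Fb* exceeds *Ff*, same-day testing at both time points always flatters the gain. A mismatch can flatter or hide it. Two separate days give no bias.

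**Step 3. Dilution.** The bias in the group mean is the average over the four patterns, and their shares are unknown. With the (3%, 2%) pair, if half the participants are same-day both times and half separate both times, the mean bias is 0.5 × 1 + 0.5 × 0 = 0.5 points. Against the 5–10% MCID that is 0.5/10 = 5% to 0.5/5 = 10%. If all are same-day both times, it is 1/10 = 10% to 1/5 = 20%.

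**Step 4. Effect on a two-sided paired test at 0.05.** The protocol enrols 80 and expects 10–20% drop-out, so 80 × 0.8 = 64 to 80 × 0.9 = 72 complete. The SD of the percentage change is not given; assume 10–15%. With no true effect and mean bias *b*, SE = SD/√n and

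P(reject) = 1 − Φ(1.96 − *b*/SE) + Φ(−1.96 − *b*/SE)

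| Mean bias *b* over all completers | SD 10% (n = 64–72) | SD 15% (n = 64–72) |
|---|---|---|
| 0 | 5% | 5% |
| 0.5 | about 7% | about 6% |
| 1 | 13–14% | 8–9% |
| 2 | 36–40% | 19–21% |

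Each row is the mean bias after dilution over all completers, so the last row needs a large share of mismatched tests or a large assumed loss. Equal conditions at both time points return the rate to 5%.

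**The case against.** The best defence is that the stated difference is small. It is one sub-maximal walk, followed by rest that Study procedures sets as a minimum and that both sections extend as needed. This stands as a reason to expect a small effect. It does not make the two time points equal.

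A second defence concerns the day mismatch. The article says that the order is standardised for consistency, and visit scheduling is often left to a full protocol or site procedure. This stands in part: differing days are permitted, not prescribed, and a matching rule may exist elsewhere. It does not reach the extra walk, which the shown text itself lays down.

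A reader might infer more than the documents support:

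- **That sit-to-stand is dropped at 12 weeks.** It precedes CPET both times.
- **That fatigue can be read from total test minutes (6 + 1 + 6 = 13 against 6 + 1 = 7).** The first walk is followed at both time points by rest and a run of lung function tests, so the sum does not measure fatigue at CPET.
- **That the false gain could equal the whole MCID.** This pairs the highest assumed loss (5%) with the lowest MCID (5%), and applies only to participants tested same-day at baseline and separately at 12 weeks.
- **That a tired baseline test sets the training load too low.** The intervention says "Aerobic exercise for 33 min on a cycle ergometer at a moderate intensity (≥ 60% Wpeak". That figure is a floor, intensity is also set by Borg rating and symptoms, and the article does not say which test supplies Wpeak.

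**Conclusion.** The point holds as a design weakness in a secondary outcome. Followed as written, the plan gives unequal earlier exertion before a same-day CPET and allows unequal day arrangements, in a paired comparison with no control group. The first part is certain from the text. The second is a permission without a stated safeguard.

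The size is unknown. Every bias in the working rests on assumed fatigue losses, and the false-positive rates rest in addition on an assumed SD of change. On those assumptions, same-day testing at both time points inflates the gain by 1 to 2 points, a mismatch moves it by between −3 and +5 points, and separate days both times give none.

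The primary outcome, protein profiles, is not touched. The article names no specific test for its further outcome of improved exercise capacity, so the point is limited to CPET results.

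**What to change.** Change the CPET entry in Study procedures and in the section on the order of assessments:

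1. **Participants without a baseline CPET yet:** CPET is done on a different day from the 6MWT and sit-to-stand tests, at both time points. The separate AiDA visit could hold it where feasible, with AiDA first.
2. **Participants whose baseline CPET is done:** repeat the same arrangement, same-day or separate-day, at 12 weeks. Enrolment began in 2022 and is still open. Moving everyone to a separate day now would create the mismatch for those with a same-day baseline.
3. **Every CPET:** record whether it was same-day or separate-day, and which tests came before it.
4. **Reporting:** give the CPET change with and without participants whose arrangement differed, or whose same-day baseline CPET followed the second walk. The second group needs this because repeating their arrangement still leaves the one-walk difference.

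The cost is a short addition to two sections, one recorded item per test and one sensitivity report. The AiDA visit becomes longer or, for some participants, there is one more attendance within the one to three visits already allowed. Some lose the option of completing all the walking, sit-to-stand and cycle tests in one day.
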